### Ethics approval

This study has been approved by the Health Research Ethics Committee at Stellenbosch University (N12/06/031) and will be conducted according to the ethical guidelines and principles of the international Declaration of Helsinki, South African Guidelines for Good Clinical Practice and the Medical Research Council (MRC) Ethical Guidelines for Research.

Permission was also obtained from the Western Cape Education Department (WCED) to offer treatment at the participants’ schools. Permission from the WCED was conditional on not disclosing the identities of the participating schools.

Consent will be obtained from parents of potential participants in the study. Informed consent and assent will be obtained by the IE when determining eligibility and prior to randomization to treatment. A participant may leave the study at any time. Study procedures as well as potential risks, benefits and treatment alternatives will be explained at the time participation in the study is discussed. Participants will be clearly informed of the voluntary nature of their participation and their right to terminate without any penalty.

The one IE, an experienced Clinical Psychologist, will screen participants for other psychopathology and will not include a potential participant if the principal diagnosis is not PTSD in response to a traumatic event.

Participating schools’ headmasters and educators will be informed that the study entails the treatment of adolescents that have experienced a trauma. In this way adolescents will not be identified in terms of the nature of their trauma. Counsellors will keep all study and personal information about participants confidential.

Participants will receive all written material in their language of choice (Afrikaans, English and Xhosa).

All counsellors will receive weekly supervision, on every participant under their care. Counsellors will have unrestricted access to the supervisor. Participants in both PE-A and SC will be informed that they can contact their counsellor between sessions should they experience a crisis or are distressed enough to need support. If a counsellor is concerned about a participant’s psychological welfare, the supervisor will arrange for a psychological assessment. Although unlikely, should significant negative emotional reactions develop that require other forms of intervention, the participant will be withdrawn from the study and will be appropriately referred.

Should the parent be unable to provide informed consent in person for the qualitative addition to the study, the following procedure will be used:Parent contacted by telephone, given information, and read the consent form. Parent will be given opportunity to ask questions. Consent via the telephone will be recorded.Teenager will be picked up for interview. Before the interview begins, the child will provide their written assent.When the teenager leaves the interview, he/she will take the informed consent form/information letter home for the parent to sign. A witness will co-sign the consent form.to be picked up for the focus group, the child must show the driver a signed copy of the consent form. The consent form will be collected at the focus group and a copy will be sent back with the teenager for the parent’s records

### Participants

Adolescents aged 13 to 18 years, who have experienced an interpersonal trauma, will be included in the study. Adolescents must present with chronic (at least 3-months) full PTSD or sub-threshold PTSD to be included. Sub-threshold PTSD is defined as having at least 1 re-experiencing symptom, at least 2 avoidance symptoms, 2 arousal symptoms and a score of 11 on the CPSS. Providing that PTSD is deemed to be the primary disorder requiring treatment, adolescents with comorbid mood disorders, anxiety disorders, substance use disorders and ADHD will also be included. Adolescents with conduct disorder, a primary substance abuse problem and psychotic disorders will be excluded.

For the qualitative study, stakeholders should have been involved in the study during the previous year (to make sure that they still remember their experiences). Stakeholders will be included even if; a) the adolescent did not complete the treatment intervention; b) the nurse did not complete the yearlong commitment; c) the nurse did not gain experience in implementing both treatment strategies; or, d) the school did not yield any recruits.

### Recruitment

Participants for the RCT will be adolescents recruited from lower socio-economic status community schools around Cape Town. A recruiter will address the children during assembly and in individual classes. The recruiter will explain the definition of a traumatic event, will describe typical events that would be considered a qualifying traumatic experience, will explain the diagnosis of PTSD and explain that this study aims to compare the effectiveness of two treatments when administered by nurses within the community (school). Adolescents who think that they could benefit from treatment will complete a PTSD screening instrument in private. Prospective participants who indicate that they have experienced a trauma and whose scores are beyond the cut-off for inclusion will be scheduled for a pretreatment assessment. For those who meet the criteria, a pre-assessment interview will be scheduled with the adolescent and their parent or guardian.

In the nested qualitative study, adolescents completing treatment in the preceding year will be invited to participate in a treatment specific focus group with similar adolescents and will participate in individual interviews. The topic guide and other standard operating procedures may be seen in (Additional file 1: Table S4 – S4c). Nurses/counsellors who had been trained in the previous year will be invited to attend a focus group (Additional file 1: Table S5 – S5c) and similarly, contact persons at school (teachers) will be invited to attend a focus group for representatives from host organizations (Additional file 1: Table S6 – S6b). All stakeholders who will have been involved in that time frame will be contacted by phone to set up an information/informed consent session for the qualitative portion of this study.

### Procedure

Counsellors will be sourced from a one-year advanced diploma in psychiatric nursing student group at the University of Stellenbosch. The definition of a counsellor for the purpose of this study will be a qualified nursing sister. Both treatments (PE-A and SC) will be provided by each of these counsellors to prevent confound of therapist effects. The nursing sisters will only be reimbursed for petrol/transport costs. Counsellors will be identified and trained every year. This will result in counsellors not seeing more than 4 participants each, thus remaining relatively inexperienced over the period of the study.

The training will be 4 days in duration, 3 days devoted to training in the PE-A protocol and the 4th-day to training in SC. The SC training will be followed by an additional 16 h of practical training. The training will culminate in the ability to implement the PE-A and SC skills following the two treatment manuals, respectively. Every counsellor will have a file with all the information needed for each participant they are treating. Counsellors will, therefore, be able to follow the treatment steps and have all the information required at the ready for every participant. Weekly supervision will occur throughout the duration of the study.

Identified individual participants enter a pre-treatment preparation phase conducted by an IE. During this time the IE will explain the study (nature of treatments, random assignment, duration of treatment, measures and follow-up procedures), obtain informed consent, and address logistical issues.

Participants will be randomly assigned to a counsellor and to a treatment condition. The randomization schedule will be created by an independent statistician and only provided to the project coordinator. The project coordinator, the only one with access to the randomization scheme, will contact the counsellor. The counsellor will be informed of the treatment condition that the client has been randomly assigned to. The counsellor will contact the school and the adolescent and set up the first appointment. Both treatments will be administered by the counsellors within the high-school setting.

Following the pre-treatment preparation, both PE-A and SC will consist of 7–14 sessions, lasting 60 min each.

The CPSS-SR will be administered at the beginning of each session in order to monitor treatment progress. From session 7, the percentage improvement from the pre-treatment baseline will be measured. When improvement reaches 70% or better, the counsellor will share the outcome with the participant and start the termination process.

The follow-up assessments will be administered by an IE blind to the treatment condition.

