**Fig. 1 Fig1:**
[figure not shown]
Study Consort Diagram, Consort diagram

A single-blind permuted block randomized control design will be used. The proposed research aims to examine the effectiveness of a psychotherapeutic intervention administered by counsellors to treat the symptoms of PTSD in adolescents exposed to trauma. The aim is to conduct a randomized controlled trial (RCT) to compare PE-A to SC to determine the comparative effectiveness in reducing PTSD and associated symptoms in adolescents.

The study will compare the efficacy of PE-A to SC. Participation will be voluntary. All participants, who meet full PTSD or sub-threshold PTSD criteria, will be scheduled for a pre-treatment assessment with Independent Evaluators (IE). The one IE will be an experienced diagnostician and clinical psychologist and the other an experienced psychiatric nurse. Adolescents will be randomly assigned on a 1:1 ratio to receive either PE-A or SC.

Treatment will consist of 7–14 sessions of either PE or SC. The number of sessions each participant receives will be based on the weekly self-report measure of PTSD symptoms (Child PTSD Symptom Scale – Self Report; CPSS-SR); however, this will range between a minimum of 7 sessions to a maximum of 14 sessions. A 70% symptom reduction is chosen as sufficient for treatment termination.

After session five, all participants will receive a mid-treatment evaluation by the IE. The IE will again assess the participants upon termination of treatment. Participants will then enter the non-treatment follow-up phase. Participants who prematurely terminate therapy (before 70% symptom reduction or 7 sessions) will undergo a post-last session assessment with the IE and will then enter the follow-up phase. Follow-up assessments will be conducted at 3-, 6-, and 12 months post-treatment and annually thereafter. The IE assessments will comprise both structured clinical interviews and self-report measures. The assessments will cover PTSD severity, related psychopathology, general psychopathology, and PTSD-related cognitions. At the 12-month follow-up, participants who receive SC and are deemed to still have clinically significant PTSD symptoms (as determined by the IE at 12-month follow-up assessment), will be offered PE-A. To add to the rigor of the study and demonstrate the long-term efficacy of the intervention, there will be annual posttreatment follow ups, dependent on the availability of funds for this purpose.

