#### General considerations for data analysis

Descriptive statistics will be gathered in order to determine if variables have a normal distribution and variables that violate assumptions of normality will be transformed. If this does not improve the normality of distribution, distribution free statistics will be used.

The study has pre-, mid-, post-treatment, three follow-up assessments and annual follow-up thereafter. This creates clustered data due to repeated measures. To examine treatment difference, generalized estimating equations (GEE) and a linear mixed-effects model approach (LMM) will be employed. Both approaches accommodate missing data. LMM will be the main analytical tool, particularly for estimating between-participant variability; GEE will be used to assess the robustness of the population parameters, such as treatment effects.

Analyses correlating the change in PTSD symptoms with each of the distress-related cognition and emotion variables at post-treatment will be performed, by pooling data across treatment conditions. Product-moment and Spearman’s rho correlation coefficients will be used.

Correlation analyses correlating the change in PTSD symptoms with each of the distress- related cognition and emotion variables at post-treatment, by pooling data across treatment conditions, will be performed. Product-moment and Spearman’s rho correlation coefficients will be used.

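### The promise that every counsellor delivers both treatments is not secured by the assignment described, and the analysis names no counsellor clustering, so precision may be wasted or misstated, though the contrast is not biased

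*Protocol article*

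**What the plan says.** The Procedure section makes the crossing of counsellor and treatment a safeguard: "Both treatments (PE-A and SC) will be provided by each of these counsellors to prevent confound of therapist effects". It then limits caseloads ("This will result in counsellors not seeing more than 4 participants each") and gives the assignment: "Participants will be randomly assigned to a counsellor and to a treatment condition". The Design section adds "A single-blind permuted block randomized control design will be used" and "Adolescents will be randomly assigned on a 1:1 ratio to receive either PE-A or SC". Block size and strata are not stated, and nothing links blocks to counsellors.

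The Participants section, in its inclusion rules for the qualitative sub-study, foresees the case where "the nurse did not gain experience in implementing both treatment strategies". That case is listed separately from the nurse who does not finish the year.

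Under General considerations for data analysis, the assessment schedule is given as the source of dependence: "This creates clustered data due to repeated measures". The linear mixed model (LMM) is the main tool, chosen particularly for variability between participants, with generalized estimating equations (GEE) as a robustness check. Neither is said to include counsellor.

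**The concern.** The article treats therapist effects as a threat and claims a design protection against them. The claim is unconditional, while the mechanism as described does not guarantee it and another section expects exceptions. The analysis section then names one source of clustering, and it is not the counsellor, although participants are randomised to counsellors and the counsellors are deliberately kept inexperienced.

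Two things are at stake. One is precision: variation between counsellors that balance or a model term could remove may stay in the error. The other is the validity of the standard error. If nurses differ in how well they deliver one treatment relative to the other, participants sharing a counsellor and an arm are correlated, and a model without counsellor does not see it. The trial wants to conclude about delivery by nurses in general, so its uncertainty should reflect variation between nurses.

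**Working it through.** **Inputs from the article.** 90 participants, 45 per arm; at most 4 per counsellor; 1:1 permuted blocks; two-tailed alpha 0.1 (Sample size section). **Assumed, not in the article:** a counsellor share of outcome variance of 0.05, 0.10 or 0.20, and total outcome SD of 1. The article gives no figure for counsellor effects that could be reproduced first.

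**Step 1: number of counsellors.** 90/4 = 22.5, so at least 23 (22 with 4 participants, one with 2).

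**Step 2: single-arm counsellors if allocation ignores counsellor.** With independent 1:1 allocation, P(one arm only) = 2 × (1/2)^m. For m = 4, 3, 2 this is 12.5%, 25%, 50%. With totals fixed at 45/45 it is 2 × C(45,m)/C(90,m), giving 11.7%, 24.2%, 49.4%. The expected number is 22 × 0.117 + 1 × 0.494 = 3.1 of 23, and simulation puts the chance of at least one at about 97%. With 3 each it is about 7 of 30 counsellors; with 2 each, about 22 of 45. Blocking 2:2 within counsellor removes every single-arm full caseload.

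**Step 3: counsellors differ overall (main effect only).** The variance of the difference in means is ρ × Σ(n1 − n0)²/45² + (1 − ρ) × 2/45, summed over counsellors, where n1 and n0 are a counsellor's numbers in the two arms. At ρ = 0.10:
- Unblocked: E(n1 − n0)² is 4 × 86/89 for a caseload of 4 and 2 × 88/89 for the last counsellor. The sum is 87.0, and 87.0/2025 = 0.0430. Variance = 0.0043 + 0.0400 = 0.0443.
- Blocked: only the last counsellor contributes, with an expected sum of 4/3. Variance = 0.0001 + 0.0400 = 0.0401.

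The loss is 1 − 0.0401/0.0443, about 9%. The simulated SDs of 0.210 and 0.201 agree. The unadjusted test keeps its size if unblocked (simulated 0.100 to 0.102 at ρ from 0.05 to 0.20). If blocked it is conservative: 0.091, 0.082 and 0.071 against a nominal 0.10.

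**Step 4: counsellors differ by arm.** Let τ be a variance component drawn separately for each counsellor in each arm. The variance is τ × Σ(n1² + n0²)/45² + (1 − τ) × 2/45. The expected sum is 221.5 unblocked and 178.7 blocked, so the multipliers of τ are 0.109 and 0.088. At τ = 0.10 the variances are 0.0509 and 0.0488, against 2/45 = 0.0444, which is about what a test without counsellor uses.

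Simulated type I error at nominal 10%, counsellor ignored:

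| τ (assumed) | Unblocked | Blocked 2:2 |
|---|---|---|
| 0.05 | about 11% | about 11% |
| 0.10 | about 12% to 13% | about 11% to 12% |
| 0.20 | about 15% | about 13% |

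Most of the inflation therefore remains under perfect blocking. It comes from the arm-specific variance, not mainly from single-arm counsellors.

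**Limit.** These simulations use one endpoint and a two-sample t-test as a stand-in for an LMM without counsellor; they do not reproduce the full longitudinal model.

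**The case against.** The strongest reply is that this is a condensed article. An independent statistician prepares the schedule, block size and strata are not reported, and a list blocked within counsellor would fit every sentence of the Procedure section. Random-effect structure is also commonly left to a fuller document. This stands in part. A reader might infer that the randomisation is known to be unblocked and that the protection has failed; the text does not support that, and the counts in step 2 hold only if allocation ignores counsellor. Nor does the sub-study rule prove unblocked allocation, since a nurse with one participant, or low recruitment, would miss one treatment under any blocking. What remains is an unconditional promise, another section that expects exceptions, and an analysis that positively names the source of clustering and leaves out the counsellor.

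A reader might also infer that therapist effects bias the comparison. They do not: counsellor is assigned at random as well as treatment, so differences between counsellors enter as chance imbalance and extra variance.

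Finally, the inflation rests on assumed values, and drawing the two arms of a counsellor independently is an extreme form of arm-specific variation. At 0.05 the excess over nominal is only about one percentage point. It is therefore not established that the intervals are too narrow: with a main effect only, they are about right or too wide.

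**Conclusion.** The point holds in limited form. The statement that each counsellor delivers both treatments is firmer than the described assignment and the sub-study rule allow, and the named clustering omits counsellor. The consequence is misstated or wasted precision, not systematic bias.

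Whether or not blocks are tied to counsellor, omitting the term has a cost once counsellors differ. At an assumed variance share of 0.10 and nominal 10%, the result is a correctly sized test with about 9% of the variance wasted (main effect, unblocked), a conservative test at about 8% (main effect, blocked), or an anti-conservative one at about 11% to 13% (arm-specific variance). The direction depends on facts the article does not give. A counsellor term is thus a concrete, cheap improvement that should be made.

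**What to change.** - Prespecify a counsellor random intercept in the LMM, with small-sample degrees of freedom, and account for counsellor in the GEE.
- Fit a counsellor-by-treatment random effect as a prespecified sensitivity analysis. With about 2 participants per arm per counsellor its variance is poorly estimable, so report it as planned and do not keep or drop it according to convergence.
- For any allocations still to be made, block treatment within counsellor, with the list held only by the project coordinator. The independent evaluator, not the counsellor, obtains consent, so concealment is not weakened. The Abstract ends the main data collection in December 2017, so this step may no longer apply; the model changes do not depend on it.
- Reword the Procedure section so that delivery of both treatments by each counsellor is an intention, state whether blocks were tied to counsellor, and reconcile it with the sub-study rule in the Participants section.

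Cost: a little more analysis work, and intervals that may widen slightly.

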#### Monitoring treatment integrity

All treatment sessions will be video recorded. Ten percent of treatment sessions will be randomly selected for protocol adherence ratings. Oversampling will take place on the sessions in which the rationale of SC or PE-A is explained to track adherence to the protocol during these critical sessions. Counsellors will make note of any mention of the trauma during the SC sessions.

#### Qualitative portion of study

Adolescents who agree to participate in the study will be interviewed by an independent evaluator and will participate in a treatment specific focus group. These interviews will be audio-recorded.

The focus groups with the nurse counsellors and school contact personnel will be conducted at Stellenbosch University by an independent clinical psychologist. A co-facilitator will record field notes and manage the audio-recording.

### The PE-A treatment group

The PE–A program consists of 7 to 14 weekly, 60 min sessions. Treatment comprises 8 modules. Homework exercises provide the opportunity for practice outside of the session. Module 1 includes presentation of the treatment rationale. Module 2 includes information gathering, identifying an index trauma, and conducting a breathing retraining exercise. Module 3 presents common reactions to trauma. Module 4 includes discussion of the rationale for in vivo exposure (confronting trauma reminders in real life), construction of the in vivo hierarchy, and assignment of in vivo homework. Module 5 includes presentation of the rationale for imaginal exposure (revisiting and recounting the traumatic memory), conducting imaginal exposure for 15 to 45 min, and processing this revisiting experience. This module is repeated for 2 to 5 sessions. In module 6, the imaginal exposure focuses on the worst moments of the trauma. Module 6 is repeated for 4 to 7 sessions. Module 7 focuses on generalization of skills learned in treatment and on relapse prevention. Module 8 comprises a “final project,” such as making a collage detailing the trauma and the gains made in treatment.

Table 1 provides a detailed outline of the PE-A treatment.

**Table 1 Tab1:** Outline of PE-A treatment, A detailed outline of the PE-A treatment

Major focus	Goals	Sessions (ideal)	Present at session
Phase 1: Psychoeducation and treatment planning			
Module 1: Treatment Rationale Tool 1: Breathing Retraining	1. Build rapport 2. Give overview of treatment 3. Introduce treatment rationale to the adolescent and the parent or guardian 4. Provide the adolescent with a tool to control anxiety	1,2	Adolescent, Guardian (Full or partial)
Module 2: Gathering Information	Gather information as the adolescent tells about the traumatic event.	1,2	Adolescent
Module 3: Common Reactions	1. Describe common reactions 2. Discuss the adolescent’s own reactions to trauma	2, 3	Adolescent, Guardian (partial)
Phase 2: Exposure			
Module 4: Rationale for Exposure Tool 2: Real Life Experiments Tool 3: Stress Thermometer	1. Review rationale for real-life experiments/In –vivo Exposure 2. Discuss how confronting feared situations reduces anxiety reactions	3,4	Adolescent, Guardian (partial)
Module 5: Dealing with avoidance. Tool 4: Construction of hierarchy for real life experiments	1. Create in vivo hierarchy 2. Choose an initial target for in vivo exposure	3,4	Adolescent, Guardian (partial)
Module 6: Recounting the trauma Tool 5: Imaginal Exposure	1. Explain why it is helpful to recount the memory of the trauma 2. Reliving the memory through writing or talking	4,5,6,7	Adolescent
Module 7: Recounting the Trauma Tool 6: Worst Moments	Process the most difficult parts of the memory	7,8,9,10, 11,12,13	Adolescent
Phase 3: Relapse Prevention and Graduation			
Module 8: Generalization and Relapse Prevention	1. Review progress 2. Discuss the efficacy of various tools acquired in therapy. 3. Introduce generalization training and relapse prevention 4. Discuss the outcome of the therapy	10,11,12,13, or 14	Adolescent, Guardian (partial)
Module 9: Graduation	1. Review Progress with Parents/Guardians 2. Celebrate accomplishments 3. Reiterate Relapse Prevention Strategies	10,11,12,13, or 14	Adolescent, Guardian (partial)
Modules 1–9: Family intervention	1. Foster relationship with guardian(s) 2. Inform the Guardian about the progress of treatment. 3. Address obstacles to treatment.	Family interventions are included in each module. Up to 3 additional sessions as necessary to meet goals of the module. To include parents with or without adolescent.	

